### 3.1. Strategies to Improve Adherence to Interventions

Adherence to intervention protocols will be constantly monitored and evaluated. Evaluation of the intervention will focus on three main domains as follows:Specific training for dental hygienists to deliver oral health promotion to children, parents, and nursery staff, focusing on tailoring key messages to the specific age at visit outlined in the care pathway, and on practical preparation for delivering interventions in the nurseries. All the procedures used to assess the outcomes of each activity will be tailored to the specific outcomes. Questionnaires will be developed by a team of sociologists and psychologists, pretested, and used before and after the interventions in order to assess possible changes in knowledge level. The questionnaires will be structured into three distinct sections: the first referring to personal characteristics, the second addressing general knowledge concerning both general and oral health, and the third focusing on awareness related to the dissemination of information and educational competencies. The Capacity-Building Framework will be used to link knowledge to actions that test the skills acquired.A toothpaste/toothbrush scheme involving free daily tooth brushing will be established for each 4- and 6-year-old child attending nursery, along with the free distribution of toothpaste/toothbrush packs to every child on at least 8 occasions (every 3 months). Daily tooth-brushing activities will be monitored by qualitative research, meaning that interviews with the educators will be used to assess the number of children who attend the kindergarten, the number of children who actually perform daily tooth brushing, the use of toothpaste, and any barriers in the implementation of the tooth-brushing scheme. The distribution of necessary materials, correct delivery of products, cost analysis showing price trends and percentage differences over the time span, and consumer price index evaluation for the given time span will be assessed as part of the cost efficiency analysis.Evaluation of clinical outcomes—caries activity levels—after implementing the daily tooth-brushing scheme. The outcomes will offer information regarding the particularities of the clinical investigation for the specific age group and the time necessary for the investigation and intervention.

### 3.2. Sample Size

The sample size calculation results in a sample of 460 children aged 4–5 years, considering the following parameters: a type I error of 0.05 (z 1 − alpha/2  =  1.96), power of 0.9 (z 1 − beta  =  1.28), standard deviation (SD) 2, a design effect of 2, and a drop-out rate of 10%. For the odds ratio, a percentage mean difference between groups was used as suggested by literature when significance is found after intervention usually measuring for caries prevalence or increment, with mixed interventions ranging from fluoride varnish and teaching how to properly brush teeth to motivational techniques and oral health education [16,17,18]. Demographics with respect to the region and age of interest were chosen.

The total sample size was calculated according to the WHO guidelines using a stratified sampling technique for examination sites in Romanian cities: Bucharest, Timișoara, Cluj-Napoca, Craiova, Iasi, Targu Mures, and the surrounding geographical areas. Data collection points will be 4 kindergartens in the Capital or metropolitan areas, 2 kindergartens in each of 2 large cities, and 1 kindergarten in each 4 villages from different geographic areas (Dobrogea, Moldova, Ardeal, and Muntenia). Metropolitan areas in Romania are Iași, Brașov, Oradea, Târgu Mureș, Cluj Napoca, Craiova, Roman, Baia Mare, Satu Mare, Timișoara, and Arad.

Data will be collected from 3 types of residential areas: metropolitan areas (150 evaluations), big cities (150 evaluations), and rural areas (100 evaluations). In metropolitan areas and big cities, 25 children will need to be evaluated in the same kindergarten.

In rural areas, more than one kindergarten can be evaluated until the desired number of evaluations is obtained for the specific region. This principle has been added because kindergarten is not mandatory in Romania and the number of children enrolled in kindergarten in rural areas is quite low in some regions of the country.

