The number of children is based on an initial calculated requirement of 415 participants, with an additional 10% (rounded up from 456.5 to 460) added to account for potential dropouts or loss to follow-up. The sample is stratified based on administrative units and locality type and randomization is ensured by using the MS Excel function. Children will be included based on the enrolment in kindergarten, consent of the parents, and assent from the child. The exclusion criteria are represented by chronic general diseases or a history of allergic reactions, the presence of fluorosis or other enamel deficiencies, and non-collaborative behavior. The selection can be seen in the flowchart in Figure 1.

The nationally representative sample will be evaluated at baseline using self-assessment tools and clinical examination. During the intervention, evaluations will be performed every 6 months.

The program is designed to deliver additional clinical prevention activities through dental hygienists, aimed at children aged four to six, a special priority being afforded to nursery establishments, in order to improve the oral health of young children and complement the established national toothpaste/toothbrush scheme. The activity flow chart can be seen in the figure below (Figure 2).

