### Study Setting

The total sample size is calculated according to the WHO guidelines using a stratified sampling technique for examination sites in Romanian cities: Bucharest, Timișoara, Cluj-Napoca, Craiova, Iasi, Targu Mures, and the surrounding geographical areas. Data collection points (Figure 3) will be 4 kindergartens in the Capital or metropolitan areas, 2 kindergartens in each of 2 large cities, and 1 kindergarten in each 4 villages from different geographic areas (Dobrogea, Moldova, Ardeal, Muntenia). Metropolitan areas in Romania are Iași, Brașov, Oradea, Târgu Mureș, Cluj Napoca, Craiova, Roman, Baia Mare, Satu Mare, Timișoara and Arad. Romania is divided into 40 counties (regional administrative sites consisting of several cities and villages), the capital, Bucharest being considered on its own. Further on, it is divided into metropolitan areas (over 250,000 inhabitants), large cities (100,000–250,000 inhabitants), small cities (less than 100,000 inhabitants), and villages (less than 5000 inhabitants). A detailed list of the study sites can be obtained from the project manager.

Children aged 4–6 years, enrolled in kindergartens in Romania will be included in the study, providing they show signed informed consent from their parents/caregivers. Parents or caregivers are responsible for signing the consent form for children and any subject may withdraw from the study at any time after recruitment. The examiners shall collect the informed consent forms prior to the examination. Before each examination, each subject will have the free will to participate by direct inquiry.

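### The stated 90% power treats the kindergartens as numerous; if 12 to 16 whole kindergartens are allocated to arms, a valid test probably falls short of it

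*Protocol article*

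**What the plan says.** Section 3.2 gives "a type I error of 0.05 (z 1 − alpha/2 = 1.96), power of 0.9 (z 1 − beta = 1.28", followed by "standard deviation (SD) 2, a design effect of 2, and a drop-out rate of 10" per cent. No numerical effect size is printed; the text says only "For the odds ratio, a percentage mean difference between groups was used as suggested by literature". Section 2 gives the resulting size: "initial calculated requirement of 415 participants, with an additional 10% (rounded up from 456.5 to 460".

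On the number of kindergartens, Study Setting lists "4 kindergartens in the Capital or metropolitan areas, 2 kindergartens in each of 2 large cities, and 1 kindergarten in each 4 villages", and the Abstract and section 3.2 give the same list: 4 + 2×2 + 4×1 = 12. Section 3.2 also sets quotas of 150 metropolitan, 150 big-city and 100 rural evaluations, states that "In metropolitan areas and big cities, 25 children will need to be evaluated in the same kindergarten", and lets rural areas add kindergartens until the quota is met. Section 3.3 selects one urban and one rural nursery per county and appears to count the two together towards a required 25 children.

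The trial is called an RCT, but the article does not say whether children or kindergartens are allocated to arms. The Excel randomisation in section 3.3 selects nurseries; it is not described as assigning them to arms.

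**The concern.** A design effect of 2 concedes that children in the same kindergarten resemble one another. Keeping 1.96 and 1.28 alongside it assumes that the between-kindergarten variance is known almost exactly, which needs many kindergartens. With 12 to 16 of them compared between two arms, only 10 to 14 degrees of freedom remain.

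The design effect also depends on cluster size, so a single value cannot fit both 12 kindergartens of about 35 children and 16 of about 26.

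Two things are at stake. A test with correct error control would have less power than stated. A test that kept 1.96 would exceed its 5% error rate.

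**Working it through.** **Inputs.** From section 3.2: two-sided alpha 0.05, power 0.90, SD 2, design effect (DE) 2. From section 2: 415 children before drop-out. Assumptions: two equal arms, kindergartens as the allocated unit, equal cluster sizes.

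**The plan's own figure.** The formula for two means is n per arm = 2 × [SD × (1.96 + 1.28) / difference]². The difference has to be back-solved, and 0.9 fits: 2 × (2 × 3.24 / 0.9)² = 103.68. Multiplying by DE 2 and by 2 arms gives 414.7, that is 415; and 415 × 1.10 = 456.5, rounded up to 460. This shows consistency and is not an independent check. The back-solving does not affect what follows, because any inputs giving 90% by this formula have a noncentrality of about 1.96 + 1.28 = 3.24.

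**Number and size of clusters.**
- Listed: 12 kindergartens, so 415 / 12 = 34.6 children each. At 25 each, 12 kindergartens would supply only 300.
- From the quotas: 150/25 + 150/25 = 12 urban, plus at least 4 rural, so at least 16; 415 / 16 = 25.9 each.
- From section 3.3: two nurseries per 25 children is about 12.5 each, so about 33 kindergartens.

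**Power with few clusters.** With K kindergartens and m = 415/K, use a noncentral t on K − 2 degrees of freedom and noncentrality 3.24 × √(2/DE). The critical value is 2.23 at 10 df and 2.14 at 14 df, against 1.96. No intracluster correlation (ICC) is printed, so DE is taken in three ways:
- held at 2;
- 1 + (m − 1)/24, if DE 2 refers to 25 children (ICC 1/24 = 0.042);
- 1 + (m − 1) × 0.030, if DE 2 refers to 34.6 children (ICC 1/33.6 = 0.030).

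| Kindergartens | df | Children each | DE held at 2 | ICC 1/24 | ICC 0.030 |
|---|---|---|---|---|---|
| 12 | 10 | 34.6 | 83.1% | 76.0% (DE 2.40) | 83.1% (DE 2.00) |
| 16 | 14 | 25.9 | 85.4% | 84.7% (DE 2.04) | 89.7% (DE 1.74) |
| 20 | 18 | 20.8 | 86.5% | 89.4% (DE 1.82) | 93.0% (DE 1.59) |
| 24 | 22 | 17.3 | 87.2% | 92.2% (DE 1.68) | 94.9% (DE 1.49) |
| 33 | 31 | 12.6 | 88.1% | 95.4% (DE 1.48) | 96.9% (DE 1.35) |

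If children are randomised individually (413 df, DE 2), power is 89.9%.

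**Error rate if 1.96 is kept.** The two-sided tail of t beyond 1.96 is 7.8% at 10 df and 7.0% at 14 df.

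**The case against.** The strongest objection is that the inputs behind any reduced figure are not fixed in the article. Allocation by kindergarten is nowhere stated, and under individual randomisation the degrees-of-freedom argument falls away. The count of 12 conflicts with the quotas and with section 3.3, and on the section 3.3 reading power runs from 88% to above 95%. The 76% figure also needs an ICC of 1/24, which the article does not give.

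All of this stands. A reader might infer that the trial's power is 76 to 83%, but the article does not support that: the range takes one side of an internal contradiction and adds two assumptions.

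Two further objections carry part of the way. The baseline-adjusted and longitudinal models in section 3.5 could recover some power. That gain cannot be sized from the article, and those models are said to handle correlation within subjects, not within kindergartens. The choice of small-sample correction is detail that an article may leave to the analysis plan, so its absence is not the fault here. The fault is that the printed power rests on a large-cluster formula while the same section lists a dozen clusters.

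The objection does not remove the case for cluster allocation as the natural reading. Brushing is offered to every eligible child attending, and educators are the ones instructed, so assigning it child by child within a kindergarten would be hard.

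**Conclusion.** The point holds conditionally. The sizes 415 and 460 reproduce, so this is not a slip in the sum; the formula does not suit the number of clusters listed.

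If whole kindergartens are allocated, equally between two arms and with equal cluster sizes, and all 415 children are analysed:
- 12 kindergartens: about 83% with the design effect at 2, or about 76% at ICC 1/24;
- 16 kindergartens: about 85% with the design effect at 2, and about 85% to 90% as the ICC goes from 1/24 to 0.030.

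Holding the design effect at 2, no count examined up to 33 reaches 90%. If the design effect falls with cluster size, about 90% is reached with roughly 20 or more kindergartens at ICC 1/24, and only just with 16 at the more favourable 0.030. If children are individually randomised, about 90% stands. The shortfall is therefore probable, but its size depends on facts the article must first settle.

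**What to change.** 1. Reconcile Study Setting, section 3.2 and section 3.3: state the unit allocated to arms, the number of kindergartens per arm, and the children per kindergarten.
2. In section 3.2, state the ICC and the cluster size behind the design effect. If kindergartens are allocated, restate power with t quantiles on (kindergartens minus 2) degrees of freedom and a design effect of 1 + (m − 1) × ICC at the reconciled count. Do not print 76 to 83% as the trial's power.
3. If kindergartens are allocated, make the between-group test account for kindergarten clustering with a small-sample correction, such as a t-test on kindergarten means or a mixed model with the Kenward–Roger correction.

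The cost is a recalculation, a line or two of text, and probably a lower stated power. No extra children are needed. If the team wants to regain power with the same 460, more and smaller kindergartens would help. The rural rule already permits adding kindergartens, at the price of more sites to run; in urban areas the rule of 25 per kindergarten would have to be revisited.

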### 3.3. Assignment of Interventions

In order to create a nationally representative sample, the public information available on the websites of all County School Inspectorates (41 counties plus the Romanian Capital) was analyzed. This process involved the evaluation of publicly available information from 4696 schools, which aided the understanding of the territorial distribution of the target population.

The national representative sample is stratified and randomized. The stratification was performed at the level of administrative units (counties), and on locality type (i.e., urban versus rural localities). For each county, the total number of pupils and the percentage of children for each of these administrative units were computed. The percentage was used to estimate how many children would have to be included in each county. The number was then divided based on locality type (i.e., urban versus rural), and the final target number of evaluations was obtained. The MS Excel’s randomization function was used for each county to select an urban and a rural nursery.

The steps of the allocation sequence are as follows:The order of the counties is decided—each collection point receives several counties and the research team can decide in which county it would be more convenient.Kindergartens in the respective county are contacted to determine their availability to participate in the study and the number of children from the target population available for evaluation.If the 2 kindergartens that are contacted together have at least 18 children (out of the required 25), data collection can begin in the respective county.

If the 2 kindergartens contacted do not have at least 18 children together, the next county on the list will be selected and the procedure returns to steps 2 and 3.

E-mails will be sent to the correspondence address provided to generate the allocation sequence. Consent in principle and an estimate of the number of children in the target population will be requested. If there is no response within the next 5 working days, the kindergarten will be called in to check that the e-mail was received in good condition (e.g., to obtain a working e-mail address or to see the status of the request).

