## 4. Expected Outcomes

The primary outcome of the trial will be the assessment of caries incidence, defined as the change in status according to the ICDAS index within the age groups. In addition, data analysis from the trial will provide information on children’s self-assessment of oral health practices and promote oral health activities for children with a focus on age-appropriate key messages and practical preparation for the implementation of the nursery intervention, which consists of a toothpaste/toothbrush scheme with free daily tooth brushing for every 4–6-year-old child attending the nursery. Depending on the region, by using the County Development Index, differences between regions will be assessed in order to establish the efficacy of the program at the national level.

Secondary outcomes will be the skills gained by dental hygienists to deliver oral health promotion to nursery nurses after specific training, and a comprehensive process of parental information and consent and validation that shapes healthy behaviours throughout life.

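### The stated site-selection schemes cannot all hold, so the sample is not shown to be nationally representative and the national-level efficacy conclusion is not supported

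*Protocol article*

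**What the plan says.** **The claim.** Section 2 (Experimental Design) states: "The nationally representative sample will be evaluated at baseline using self-assessment tools and clinical examination". Section 3.3 (Assignment of Interventions) repeats it: "The national representative sample is stratified and randomized". Section 4 (Expected Outcomes) says that, using the County Development Index, "differences between regions will be assessed in order to establish the efficacy of the program at the national level".

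**The site selection.** Section 2 says nurseries are chosen by the pathfinder technique. The details then come in three forms:

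- **Collection points** (Study Setting, repeated in Section 3.2): four kindergartens in the capital or metropolitan areas, two in each of two large cities, and one in each of four villages.
- **Quotas** (Section 3.2): "Data will be collected from 3 types of residential areas", with 150 evaluations in metropolitan areas, 150 in big cities and 100 in rural areas. Each metropolitan or big-city kindergarten contributes 25 children. Rural areas may use extra kindergartens to reach their number.
- **County draw** (Section 3.3): strata are county by urban or rural. Enrolment shares set the county targets: "The percentage was used to estimate how many children would have to be included in each county". A spreadsheet randomisation function picks one urban and one rural nursery for each county. The team then decides which of its counties is more convenient. It moves on to the next county if the two kindergartens together hold fewer than 18 of the 25 children required.

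**The locality types.** Study Setting names four: metropolitan areas, large cities, "small cities (less than 100,000 inhabitants"), and villages. The collection points and quotas cover only metropolitan areas, large cities, and villages or rural areas.

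**The concern.** National representativeness depends on the sampling frame and on how units are drawn from it. Here the reader cannot tell which frame applies. The three descriptions differ in strata, number of kindergartens and number of children, and whether a small-city child can enter depends on which one is followed. In the county draw, chance operates only within a county; the county itself is chosen for convenience.

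This matters because Section 4 draws a conclusion for the country, and Section 5 (Discussion) says results will be reported to national stakeholders and government bodies and calls the program a pilot for national implementation. Such readers would take the national wording at face value.

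**Working it through.** **1. The plan's own total.** Section 2 gives 415 plus 10%: 415 × 1.10 = 456.5, rounded up to 460. This reproduces. The 415 itself cannot be rebuilt, because Section 3.2 gives no numeric effect size, but that is not needed here. The scheme actually used should deliver 460 recruited children.

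**2. Collection points.** 4 + (2 × 2) + (4 × 1) = 12 kindergartens, reading the first figure as four in total, as the Abstract does. At 25 children each, the eight urban sites give 8 × 25 = 200. If the villages also gave 25 each (an assumption), the total would be 12 × 25 = 300.

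**3. Quotas.** 150 + 150 + 100 = 400. This is 415 − 400 = 15 below the requirement before dropout and 460 − 400 = 60 below the recruitment target. At 25 per urban kindergarten, 150 / 25 = 6 metropolitan and 150 / 25 = 6 big-city kindergartens are needed. The list has 4 and 4. The quotas and the collection points therefore conflict even within Section 3.2.

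**4. County draw.** Section 3.3 counts 41 counties plus the capital, so 42 units. (Study Setting says 40 counties plus the capital, a smaller discrepancy.) One urban and one rural nursery per unit gives 42 × 2 = 84 nurseries if every unit is used. At 25 per unit that is 42 × 25 = 1050 children; at the minimum of 18 it is 42 × 18 = 756. To reach 460 at 25 per unit, only 460 / 25 = 18.4 units would be used, which is fewer than half.

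**5. Inside Section 3.3.** Targets proportional to enrolment would differ between counties, yet the start rule uses the same 25 in each. That 25 is for two kindergartens together, whereas in Section 3.2 it is for one urban kindergarten.

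| Description | Strata | Kindergartens | Children |
|---|---|---|---|
| Collection points | metropolitan, large city, village | 12 | 300 (assuming 25 at every site) |
| Quotas | metropolitan, big city, rural | 6 + 6 urban, rural number open | 400 |
| County draw, all units | county × urban/rural | 84 | 756 to 1050 |
| Planned sample size | – | – | 460 |

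No row gives 460.

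**6. Small cities.** The collection points and the quotas give them nothing. The county draw neither names nor excludes them: its urban stratum is not restricted to large cities.

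**7. Regional comparison.** The listed collection points lie in at most 4 + 2 + 4 = 10 localities, because the two large cities hold two kindergartens each. Extra rural kindergartens could add to this. On the listed points, then, at most 10 localities carry the comparison by County Development Index.

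**The case against.** The strongest reply is that the county draw is a list of candidates, not of sites. Each collection point receives several counties and works down them, so 84 was never a planned number, and setting it against 12 compares a possible frame with planned sites. That is fair: 84 is an upper bound. It does not remove the conflict, because on this reading the county that supplies the children is the one the team finds convenient, so the enrolment percentages no longer decide how many children come from where.

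Three stronger readings are tempting and are not supported:

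- *Small cities are never sampled.* This is true of the collection points and the quotas only. The urban stratum in Section 3.3 could yield a small-city nursery.
- *The efficacy result is biased.* Section 1.1 tests an effect on caries status. An unrepresentative sample does not by itself distort a comparison between arms drawn from it; it limits extrapolation.
- *The rural share of 100 / 400 = 25% is wrong.* The enrolment percentages are not printed, so no discrepancy can be shown.

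It is also fair that the 18-child rule is mild (18 / 2 = 9 per kindergarten on average), that kindergartens which do not answer are telephoned, and that Section 3.2 makes allowance for low rural enrolment. Any tilt towards larger kindergartens may be small and cannot be sized from the article. A full protocol may hold a site list, and the article says one is available, but a list of sites would not settle which of the printed rules produced it.

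**Conclusion.** The point holds as a matter of internal contradiction and generalisability. The collection points (12 kindergartens), the quotas (400 children, needing 12 urban kindergartens against 8 listed) and the county draw (up to 84 nurseries) cannot all be followed, and none delivers 460. One of the four locality types has no collection point or quota, and the county used is a convenience choice. The sample is therefore not shown to be nationally representative, and efficacy at national level is not supported. The regional comparison rests on at most 10 localities if the listed points are the sites.

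The arithmetic assumes four metropolitan kindergartens in total and 25 children per urban kindergarten; the 300 also assumes 25 per village, and the 84 assumes that all 42 units are used. The contradiction between quotas and collection points, and the shortfall against 415 and 460, need neither of the last two assumptions.

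**What to change.** 1. Keep one sampling scheme. State its strata, the kindergartens per stratum and the children per stratum, summing to the planned 460, and remove the conflicting text from Study Setting and Sections 3.2 and 3.3. State whether small cities fall within it.
2. Delete the claim of national representativeness in Sections 2 and 3.3, and describe the sample by how sites are actually chosen, including the convenience step and the 18-child rule if they remain.
3. In Section 4, limit the efficacy conclusion to the locality types sampled, and label comparisons by County Development Index as descriptive.

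Items 2 and 3 cost only wording. Item 1 also means settling the site and child numbers, since none of the printed schemes reaches 460. The price is a narrower claim.

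Moving part of the big-city quota to small cities and weighting by county enrolment is not a workable substitute. It leaves the total at 400, and with so few sites most counties would have no observations to weight.

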Currently, oral health care for young children is insufficient. For this reason, it is important to create new medical teams and provide comprehensive training for dental hygienists. Dental hygienists play a very important role in oral health promotion and disease prevention, being in close contact with patients in clinical and community settings. They are able to provide education and early detection of oral diseases, deliver preventive measures, and create individual oral care plans. By having close relationships with patients, starting from very young ages, dental hygienists are able to influence long-term health behaviors and ensure consistent dental check-ups. Their role is even more important in preventive interventions for children in underprivileged communities, thereby reducing oral health inequalities and enhancing overall health status. Therefore, dental hygienists are of great importance in sustaining oral health but can also help to increase the importance of prevention within the health care systems. Until recently, Romania has lacked baseline data regarding the oral health status of children. A contemporary assessment is therefore mandatory in order to advance scientific understanding and allow for the development of adequate public health policies. During 2019–2020, the National Oral Health Survey evaluated a significant sample of children aged 5, 6, and 12 years, gathering baseline data on oral health according to the WHO guidelines. The data were used to estimate the distribution and severity of dental caries, the need for community-oriented disease prevention and health promotion, and the nature and urgency of the oral health interventions required. The survey also established how younger age groups can be reached and evaluated. Data show that only 14% of 6-year-old children have dmft (decayed-missing-filled teeth) 0 and the SiC index (significant caries index) of the same sample is 9.83. The high prevalence and severity of dental caries, significant oral health inequalities, and poor utilization of and access to services highlighted the need for a child oral health program. These findings are common to many other countries in the region, as well as other developing regions. Oral health status is strictly related to common risk factors, such as socio-economic status, education, and access and utilization of health care services [29,30,31,32,33]. Low socio-economic status leads to a decreased use of dental services, influenced by a lack of resources, treatment costs, and access to health care [30,34,35,36,37]. This is of great importance mainly in developing countries due to financial constraints [38], where discrepancies between high- and low-income families can lead to inequalities in dental care. Thus, children from low-income families tend to seek dental care mainly for curative and emergency treatment and usually do not benefit from health promotion or preventive care [4].

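### The area quotas add to 400 children, below both the 460 to be enrolled and the 415 required for 90% power, and the site schemes do not agree with either count

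*Protocol article*

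**What the plan says.** Section 2 (Experimental Design) gives the requirement: "The number of children is based on an initial calculated requirement of 415 participants". The enrolment figure is then obtained from that requirement by a margin for losses, described in these terms: "with an additional 10% (rounded up from 456.5 to 460) added to account for potential dropouts or loss to follow-up". Section 3.2 (Sample Size) repeats 460. It lists a two-sided type I error of 0.05 (z = 1.96), power 0.9 (z = 1.28), SD 2, design effect 2 and 10% drop-out. For the effect it says only: "For the odds ratio, a percentage mean difference between groups was used". It prints no numerical difference, odds ratio or allocation ratio.

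The same section then gives the recruitment plan:

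- Quotas: "metropolitan areas (150 evaluations), big cities (150 evaluations), and rural areas (100 evaluations".
- Sites, as in Study Setting and the abstract: "4 kindergartens in the Capital or metropolitan areas, 2 kindergartens in each of 2 large cities, and 1 kindergarten in each 4 villages".
- Children per urban site: "In metropolitan areas and big cities, 25 children will need to be evaluated in the same kindergarten".
- Rural areas may use more than one kindergarten, until the number wanted for the region is reached.

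Section 3.3 (Assignment of Interventions) describes selection by county, with one urban and one rural nursery drawn in each. The starting rule is: "If the 2 kindergartens that are contacted together have at least 18 children (out of the required 25), data collection can begin".

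**The concern.** The stated power belongs to 415 analysed children. The quotas are what the field teams at the partner universities will recruit to, and meeting them exactly leaves the trial short of its own requirement before any child is lost. The site list implies a smaller number again, and the county scheme attaches the figure of 25 to a different unit. The article therefore carries several sizes for one trial and claims 90% power for a size that the recruitment plan does not deliver. A null result would then be read as coming from a better-powered trial than the one conducted.

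**Working it through.** **1. The plan's own figures.** The loss step reproduces: 415 × 1.10 = 456.5, rounded up to 460. In the other direction, 460 × 0.90 = 414, essentially the requirement.

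The base figure of 415 cannot be reproduced from printed inputs alone, because no difference is given. Solving backwards for two equal arms, with 415 as the total including the design effect:

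- Total = 2 arms × DE × 2(1.96 + 1.28)² × SD² / δ²
- With DE = 2, SD = 2, δ = 0.9: 2 × 2 × 2 × 10.4976 × 4 / 0.81 = 414.7, i.e. 415.

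So δ is about 0.9 on that reading. Other readings of 415 give other values:

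- 0.636 if 415 is a two-arm total without the design effect, or a per-arm figure with it;
- 0.45 if 415 is per arm without it.

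**2. Quotas.** 150 + 150 + 100 = 400. That is 460 − 400 = 60 short of enrolment (13%) and 415 − 400 = 15 short of the requirement.

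**3. Site list.** 4 + (2 × 2) + 4 = 12 kindergartens.

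| Stratum | Sites listed | Children | Quota |
|---|---|---|---|
| Capital or metropolitan | 4 | 4 × 25 = 100 | 150 |
| Large cities | 4 | 4 × 25 = 100 | 150 |
| Rural | 4, more allowed | 100 (the quota) | 100 |
| Total | 12 or more | about 300 | 400 |

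At 25 per site, each urban quota needs 150 / 25 = 6 kindergartens; 4 are listed.

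**4. County scheme.** Section 3.3 applies 25 to two nurseries in a county together, whereas Section 3.2 applies it to a single urban kindergarten. Section 3.3 prints no total, so it does not restore 460.

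**5. Power.** With δ = 0.9 (assumed), SD 2, DE 2 and equal arms, the effective number per arm is N/4, and power = Φ(0.9 / (2√(2/(N/4))) − 1.96).

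| Children analysed | How reached | Power |
|---|---|---|
| 415 | stated requirement | 90.0% |
| 400 | quotas filled, no loss | 88.9% |
| 360 | 400 enrolled, 10% lost | 85.5% |
| 300 | site list, no loss | 78.7% |
| 270 | 300 enrolled, 10% lost | 74.4% |

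The difference detectable with 90% power rises from 0.90 at 415 to 0.97 at 360 and 1.12 at 270.

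Provided 415 is the total required for 90% power and the design effect is unchanged, these powers depend only on the ratio of N to 415: power ≈ Φ(3.24√(N/415) − 1.96). For N = 360 this is Φ(3.24 × 0.931 − 1.96) = Φ(1.06), again about 85.5%. Within that reading, the exact difference therefore matters little to the loss of power.

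**6. Design effect.** A value of 2 at 25 children per kindergarten corresponds to an intracluster correlation of (2 − 1)/(25 − 1) = 0.042. If the number per kindergarten changes, a design effect of 2 no longer follows from that correlation.

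**The case against.** **If the 400 are children retained after losses, the gap is small.** This is fair: power would be 88.9%. But 400 is still below 415, and Section 3.2 goes on to speak of children to be evaluated, with no sign that the quotas are net of loss.

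**The figure of 300 is not a proven ceiling.** This stands. A reader might infer that the trial can reach only 300 children. Section 3.3 gives several counties to each collection point, and if the listed sites are such points, 12 of them do not cap recruitment at 300. The site figures are not shown and a detailed site list is held by the project manager. The 300 is the natural reading of Section 3.2 and Study Setting, and it conflicts with the quotas; more than that cannot be said. The rural clause does not help, because it stops at the rural quota.

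**The starting rule is not a reduced target.** A reader might take 18 out of 25 as planned under-recruitment. The text makes it a threshold for beginning collection in a county and sets no final number.

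**Stronger statements about power are not supported.** A reader might:

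- treat 0.9 as the sponsor's chosen difference, although it is back-solved and other readings of 415 fit;
- add a penalty for few clusters, although the article does not state whether whole kindergartens are allocated, and 400 children at 25 per site would not be 12 clusters;
- call SD 2 too small from the survey result that "only 14% of 6-year-old children have dmft (decayed-missing-filled teeth) 0 and the SiC index (significant caries index) of the same sample is 9.83". Those are cross-sectional dmft figures at age 6. The primary outcome is a change in ICDAS status, and its SD cannot be derived from the article.

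**A condensed article may leave details to a fuller plan.** That covers omissions. Here the figures are printed and they disagree.

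**Conclusion.** The concern holds as a contradiction between counts. That the quotas total 400, below both 460 and 415, is plain addition and needs no assumption beyond reading evaluations as children. The 12-kindergarten list (about 300 children on its natural reading) and the county scheme are further conflicts to reconcile.

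The power consequence is conditional on 415 being a two-arm 1:1 total that includes the design effect of 2, with an implied difference of about 0.9. The loss is modest if the quotas are met (about 86% after 10% loss) and material only if the site list is the true plan (about 74%). The effect description is also incoherent as written: it speaks of an odds ratio, while the calculation lists an SD, which belongs to a difference in means.

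**What to change.** Choose one sample size and one site scheme, and make Section 2, Study Setting, Section 3.2 and Section 3.3 agree, including whether 25 children applies to one kindergarten or to two together. Then either:

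- keep the 400 quotas and restate the power, about 86% after 10% loss on the assumptions above; or
- set quotas that add to 460, with a site list that can supply them.

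In both cases the sponsor should state the difference and effect measure actually used and the allocation ratio, and remove the mismatch between odds ratio and SD. The design effect of 2 should be checked against the final number of children per kindergarten.

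The cost is wording and one recalculation, with a less favourable stated power if 400 is kept. Extra kindergartens are a cost only if 460 is kept and the final scheme cannot supply it from the listed sites.
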